#### Methods against bias

The proposed study requires several methods to avoid bias.

Selection bias: The randomisation procedure is the gold standard to avoid this bias. Random numbers will therefore be generated in advance. The randomisation procedure will be controlled by comparing the two groups with regard to possible confounders, i.e. age at the time of trauma, gender, educational level, diagnosis, cognitive status and trauma severity.

Detection bias: The baseline assessment is done before randomisation to avoid this bias. In addition, the therapists will not collect any outcome data at posttest and follow-up. This will be done by blinded members of the research team (clinical psychologists or psychiatrists or advanced master students in clinical psychology).

Performance bias: To counteract this bias, the standardisation procedure (manual, extensive training, documentation of sessions, supervision) is established.

Attrition bias: Statistical analysis will include techniques to minimise possible attrition bias, i.e. intention-to-treat analysis and imputing missing data. In case of drop-outs, it is intended to continue data collection whenever possible.

#### Handling of missing values and drop-outs

A complete data set is available if all three test times (pretest, posttest, follow-up) have been performed. A drop-out can occur, (1) if the participant does not complete the pretest, (2) decides after information or after randomisation against participation, or (3) starts with the treatment, but discontinues it.

If less than 20% of the items of one self-report instrument are missing, missing values are imputed by the mean of the scale of this participant. If a whole scale is missing, the value will be imputed by the expectation-maximation (EM) algorithm.

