#### Sample size

Previous studies on PTSD treatments found a large mean effect size for PTSD outcomes (controlled *d* = 0.8 with a supportive control group) [26]. Studies on LRT also found a large mean (pre-post) effect size in older individuals with a mental disorder (in most studies depression) (g = 1.3; 19). We rest our sample size calculation on the conservative assumption of a medium-to-large effect size (d = 0.7, corresponds to f = 0.35). The sample size was calculated using G*Power 3.1.0 [27]. Given an α = 0.05 and a test power 1-β = 0.80, a total sample size of *n* = 50 (each group *n* = 25) is required. We assume a rather conservative drop-out rate of about 40% from enrolment to follow-up. Thus, we propose to start with 80 participants at enrolment (i.e. 40 in the LRT and 40 in the control group).

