### Randomisation

After providing informed consent and receiving a baseline assessment, the participants will be individually assigned to a group at random. The allocation ratio for randomisation into either the treatment or control group is 1:1. The randomisation will be performed by a randomization list that was generated by a computer programme (RandList) beforehand, independently operated by the principal investigator at the University of Siegen, Germany, who does not have any personal contact with the participants. The results of the randomization will be sent to the study coordinator in Jerusalem, Israel, who will contact the therapist to explain the next steps.

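### Filling each wholly missing scale with one EM value, then running ANOVA with no allowance for imputation, understates standard errors or shrinks the effect; the size depends on how much is missing

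*Protocol article*

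**What the plan says.** The protocol article fixes two imputation rules under Handling of missing values and drop-outs. Where fewer than 20% of the items of an instrument are missing, they are replaced by the participant's own scale mean. For a wholly missing instrument the rule is: "If a whole scale is missing, the value will be imputed by the expectation-maximation (EM) algorithm". The wording describes one value per missing scale.

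Under Methods against bias, the stated protection against attrition bias is "intention-to-treat analysis and imputing missing data", together with an intention to keep assessing drop-outs where possible.

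Under Statistical analysis, ANOVA comes first, for the primary and secondary endpoints. Its listed covariates are age at trauma, gender, education, cognitive status and trauma severity. Pretest score is not among them. Growth curves and multivariate analyses follow.

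Under Sample size, the plan expects a "drop-out rate of about 40% from enrolment to follow-up". The article does not mention multiple imputation, a variance correction or the variables in the EM model.

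**The concern.** A single EM fill-in adds rows to the data set but no information. The predicted scores sit on the fitted line, and ANOVA then counts them as if they had been measured. Two outcomes are possible, and which one applies depends on a detail that the article does not give.

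- **Arm in the EM model.** The treatment difference is estimated without bias. The residual variance is too low and the sample size too high, so the standard error is too small and the null hypothesis is rejected too often.
- **Arm not in the EM model.** The filled-in scores ignore treatment, pull the two groups together and shrink the estimated effect.

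The article states this rule for the intention-to-treat analysis of its primary endpoints. It is therefore a stated choice, not a detail left for an analysis plan. Naming the EM variables would only decide which of the two problems occurs.

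**Working it through.** **The plan's own figures.** Inputs from Sample size: "Given an α = 0.05 and a test power 1-β = 0.80", "medium-to-large effect size (d = 0.7, corresponds to f = 0.35"), 50 participants needed, and "we propose to start with 80 participants at enrolment (i.e. 40 in the LRT and 40 in the control group"). Randomisation is 1:1.

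- A repeated-measures between-group F test has noncentrality N·m·f²/(1+(m−1)r). With N = 50, m = 2, f = 0.35 and an assumed r = 0.5, this is 50×2×0.1225/1.5 = 8.17. On 1 and 48 degrees of freedom the power is 0.7996, so 50 is reproduced. A two-sided t-test at one time point would need 68.
- Attrition: 80×0.6 = 48, and 50/80 = 62.5% retained, which is 37.5% loss. The 80 fits only if about 40% is read loosely.

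**Assumptions for the check (not in the protocol).** SD 1; a fraction q of follow-up scores missing completely at random, equally in both arms; correlation r between waves of 0.5 or 0.7; EM without added residual noise. In the formulas the missing score is predicted from pretest alone. n = 40 per arm.

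**A. Arm in the EM model, unadjusted follow-up comparison.**

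- True variance of the difference: 2[(1−r²)/(n(1−q)) + r²/n].
- Variance that the ANOVA reports: (2/n)[(1−q) + q·r²].
- For q = 0.4 and r = 0.5 the true variance is 2[0.75/24 + 0.25/40] = 0.075, SE 0.274. The reported variance is 0.05×[0.6 + 0.1] = 0.035, SE 0.187. The ratio is 0.68.
- Type I error is about 2Φ(−1.99×ratio) = 2Φ(−1.36), or 17%.

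| Missing | r | True SE | Reported SE | Ratio | Type I error |
|---|---|---|---|---|---|
| 10% | 0.5 | 0.233 | 0.215 | 0.92 | 6.6% |
| 10% | 0.7 | 0.230 | 0.218 | 0.95 | 5.9% |
| 20% | 0.5 | 0.244 | 0.206 | 0.85 | 9.2% |
| 20% | 0.7 | 0.237 | 0.212 | 0.89 | 7.6% |
| 40% | 0.5 | 0.274 | 0.187 | 0.68 | 17.4% |
| 40% | 0.7 | 0.259 | 0.199 | 0.77 | 12.5% |

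Simulations, some with only 20% missing at posttest so that posttest also predicts, gave 12-18% at 40% missing, 7-10% at 20% and 4-8% at 10%.

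**B. The same, under other forms of the analysis.**

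- Pretest score added as a covariate, q = 0.4, r = 0.5: true variance 2×0.75/24 = 0.0625, SE 0.250. Reported variance is 0.05×0.75×(48−3)/(80−3) = 0.0219, SE 0.148. The ratio is 0.59 and type I error about 24%. Simulations gave 22-25%.
- Repeated-measures between-group test over three waves, 20% missing at posttest and 40% at follow-up: 7-8% by simulation. It is lower because the complete pretest enters the average.

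**C. Arm not in the EM model.**

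- The expected difference is (1−q)·d: 0.6×0.70 = 0.42 at 40% missing and 0.8×0.70 = 0.56 at 20%.
- If posttest is half as often missing as follow-up, the observed posttest scores carry part of the effect. The estimate is then 0.47-0.50 at 40% and about 0.59 at 20%.
- Type I error was about 5% in simulation.

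**D. Comparison with valid methods (40% missing, r = 0.5, pretest-adjusted).**

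- Multiple imputation with arm (30 imputations, Rubin's rules): mean SE 0.258 against a true 0.254, type I error 4.7%, estimate 0.71, power 76%.
- Complete cases: SE 0.25, type I error 5.3%, power 78%.
- Single EM with arm: apparent power about 95%. The excess over 76-78% is spurious.

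**The case against.** The strongest reply concerns size, and most of it stands.

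- **A reader might infer that 40% of follow-up scores will be filled in.** The article does not say so. Its definition of drop-out includes people who do not complete the pretest or who decline after being informed, and who may never be randomised. It also includes those who stop treatment, whose assessment is to continue where possible. Under Consent, participants given alternative treatment stay in follow-up and analysis. The plan itself calls the figure "rather conservative". Hence 40% is close to an upper bound, and the results at 10% and 20% matter as much.
- **A reader might take 22-25% as the error rate of the planned analysis.** That figure needs pretest score as a covariate, which the listed covariates do not include. The form of ANOVA is not fixed, and a repeated-measures between-group test gives only 7-8%.
- **A reader might conclude that all p-values are invalid.** If arm is left out, the test keeps its size under the null. The damage is to the estimate and its interval.
- **A reader might add that scores would be assigned after death, given a mean age of 89.** That age describes social-club attendees in 2020, not the enrolled sample. No mortality figure is given, and death is not among the listed drop-out routes. The documents do not support the point.

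It can also be said that the EM variables belong in an analysis plan, that residual noise might be added, and that growth curves can use observed scores without imputation. The first leaves the single-value rule in place. Noise in a single imputation would lessen the understatement but not remove it. The growth curves come second, and no analysis is exempted from the fill-in.

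**Conclusion.** The whole-scale rule is wrong as written, and it should be fixed before analysis. A single EM value per missing scale, followed by ANOVA without allowance for imputation, either understates the standard error (arm in the model) or shrinks the effect (arm left out).

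The consequence ranges from slight to serious. In the first case, an unadjusted follow-up comparison at a nominal 5% moves from 4-8% at 10% missing to 12-18% at 40%. In the second, the loss is (0.70−0.56)/0.70 = 20% of the effect at 20% missing and (0.70−0.42)/0.70 = 40% at 40% missing, or somewhat less where posttest is observed.

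That the filled-in values are analysed as observed is inferred from the single-value wording and the absence of any correction. The sizes rest on data missing completely at random and on the assumed correlations. Data missing not at random would add bias that none of these methods removes.

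**What to change.** Replace the sentence on wholly missing scales with one of the following:

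1. A likelihood-based mixed model (arm by time) on all observed scores of all randomised participants, with no filling-in of missing scales.
2. Multiple imputation with arm, pretest and posttest scores in the imputation model, with estimates and standard errors combined by Rubin's rules.

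Keep the person-mean rule for single items. The change is one sentence and uses standard software. The price is wider confidence intervals: in the pretest-adjusted example at 40% missing, the standard error goes from 0.149 to 0.258, which matches the true sampling error of 0.254.

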#### Data handling

There are three types of data that is developed or collected in this study: the LRT manual, the “life book” and the assessment data (pre, post and follow-up). The LRT manual will be published by an international publisher in English with the aim that it will be used throughout the world in the treatment of Holocaust survivors and other older, multiply traumatised individuals.

The life book is a folder that the patient fills with photos, important written (positive and negative) memories from all life phases, the trauma narratives, helpful thoughts, personal and social strengths, information about the family etc. This life book will remain in the possession of the patients and will *not* be analysed. It is a by-product of the therapy. However, if the patient wishes, he/she can submit parts of this life book as a testimony to Yad Vashem (www.yadvashem.org), an Israeli institution that preserves a database of Holocaust victims and their testimonies. The participants might wish to pass information on his/her biography to the public, but we do not request it, it is the autonomous decision of each individual Holocaust survivor.

The assessment data (information on symptoms) must also be considered very sensitive data. Therefore, the data will be stored in an anonymous form. Storage and backup will be ensured during the project by the principal investigator in cooperation with the representative of the IT department of the Centre for Information and Media Technology (ZIMT) of the University of Siegen. The long term archiving will be done in the data repository of the ZIMT.

The data and all associated documentation will be stored for a minimum of 10 years after the completion of the study, including the follow-up period.

### Communication between German and Israeli teams

We plan to communicate between the German and Israeli team in three ways. First, we plan monthly skype meetings to discuss ongoing, day-to-day issues such as recruitment and data entry. Second, there will be one face-to-face meetings per year, either in Germany or in Israel. These meetings will be used to discuss questions that have emerged in relation to supervision, adherence to the treatment manual, training of new student assistants in data entry, interpretation of pre-post analyses and pre-follow-up analyses etc. Third, data exchange between Israel and Germany is ensured via the web-based data entry system.

### Regulatory issues

This is an RCT with individuals in need of special protection and, thus, requires particular ethical considerations.

#### Ethics approval

The approvals of the ethics committee of the German Association of Psychology (Deutsche Gesellschaft für Psychologie, DGPs, 11/01/2016, ref.: SF_112015) and the ethics committee of the Hebrew University of Jerusalem, School of Social Work (15/05/2017) have been obtained. The study will be conducted in accordance with principles enunciated in the current Declaration of Helsinki, the guidelines of good clinical practice (GCP) issued by the International Conference on Harmonisation (ICH) and the German and Israeli regulatory authority’s requirements.

Participation in the study is voluntary. There are no negative consequences for non-participation or dropping out. Individuals who refuse participation or drop out will get medical and psychosocial care as usual. While ethical problems might arise due to randomisation, the control group is a social support group, so participants in both study groups will benefit if they enrol in the study.

#### Consent

Consent to joining the study will be requested from each participant only after a full verbal and written explanation has been given, an information leaflet offered and time allowed for consideration; such declarations of consent will be signed. The right of the participant to refuse to participate without giving reasons will be respected.

After the participant has entered the study, the clinician will remain free to provide alternative treatment to that specified in the protocol at any stage if he/she feels it is in the participant’s best interest, but the reasons for doing so will be recorded. In these cases, the participants remain within the study for the purposes of follow-up and data analysis. All participants are free to withdraw at any time from the treatment without giving reasons and without prejudicing further treatment.

#### Confidentiality

The principal investigator will preserve the privacy of participants taking part in the study and is registered under the Data Protection Act. Assessment and processing of all personal data is done pseudonymised, i.e. with a number and without indication of the participant’s name. A coding list on paper, which is accessible only to the study management, is used to link names with numbers. It will be destroyed after termination of data collection, whereupon the data will become anonymised.

#### Audits

The study may be subject to inspection and audit by regulatory bodies to ensure adherence to GCP, national law, and regulatory requirements.

#### Adverse events

Adverse events (AEs) are any negative medical or psychological occurrence in the study subject, e.g. worsening of symptoms. Serious adverse events (SAEs) are any negative and unexpected medical or psychological occurrence or effect that: results in death; is life-threatening (refers to an event in which the subject was at risk of death at the time of the event; it does not refer to an event which hypothetically might have caused death if it were more severe); necessitates hospitalisation, or prolongation of existing inpatients’ hospitalisation; results in persistent or significant disability or incapacity; is a congenital anomaly or birth defect.

Medical or psychological judgement will be exercised in deciding whether an AE is serious in other situations. Important AEs that are not immediately life-threatening or do not result in death or hospitalisation, but may jeopardise the subject or may require intervention to prevent one of the other outcomes listed in the definition above, will also be considered serious.

Reporting procedures: All adverse events will be reported. Depending on the nature of the event, the reporting procedures below will be followed. Any questions concerning adverse event reporting must be directed to the principal investigator in the first instance.
Non serious AEs: All such events, whether expected or not, will be recorded.Serious AEs: An SAE form will be completed and faxed to the principal investigator within 24 h. However, hospitalisations for elective treatment of a pre-existing condition do not need reporting as SAEs.

The principal investigator will assess whether the event is:
‘Related’, i.e. resulted from the administration of any of the research procedures; and‘Unexpected’, i.e. an event that is not listed in the protocol as an expected occurrence.

Reports of suspected related and unexpected SAEs (SUSARs) will be submitted within 15 days or within 7 days for fatal or life-threatening SUSARs, respectively, of the investigator becoming aware of the event to the Ethics Committee.

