#### Recruitment

The participants will be recruited from ten centres of Amcha in Israel. Mean age of Holocaust survivors attending the social club at Amcha centres is currently (in the year 2020) 89 years, the youngest were born in 1945. About 30% were born between 1935 and 1945 (now 75–85 years old), 50% between 1925 and 1935 (now 85–95 years old) and 20% were born before 1925 (now over 95 years old).

Study participants will be recruited from current and new social club members. During the time of the research project, there will be active advertisements in the community and at medical practices in order to introduce Amcha, its social clubs and the study treatment. The fact that Amcha is present in 15 cities across Israel, has a very good reputation in the country, and is working with other medical institutions, makes the proposed study highly feasible.

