#### Assessment of safety

Participants will be regularly screened for suicidality. In case of increased suicidality - although not expected - participants will be taken out of the study by the research team. For safety and for keeping an overview over the study, a case report form (CRF) will be completed after each information, assessment or therapy session. The CRF contains checklists, test results, information about the participant (other therapies, medications, problems etc.), adverse events, date of the assessments and name of the investigators.

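### The SAE definition includes unexpectedness, which the same section assesses again later; as written, a serious but expected event gets no SAE form and no 24-hour notice

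*Protocol article*

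**What the plan says.** All of the key wording is in the Adverse events section of the protocol article.

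- **AE definition:** "Adverse events (AEs) are any negative medical or psychological occurrence in the study subject, e.g. worsening of symptoms". It sets no condition about expectedness.
- **SAE definition:** "Serious adverse events (SAEs) are any negative and unexpected medical or psychological occurrence or effect that: results in death", followed by the other usual outcomes (threat to life, hospital admission or a longer stay, lasting disability, birth defect).
- **Judgement clause:** other events may be classed as serious by judgement. The clause is worded for "Important AEs that are not immediately life-threatening or do not result in death or hospitalisation, but may jeopardise the subject".
- **Reporting:** "All adverse events will be reported", by a procedure that depends on the type of event. For the lower class: "Non serious AEs: All such events, whether expected or not, will be recorded". For SAEs, a form goes to the principal investigator within 24 hours. The one stated exemption is planned admission for a condition the participant already had.
- **Later assessment:** the principal investigator then decides whether the event is related and whether it is unexpected, the latter meaning "an event that is not listed in the protocol as an expected occurrence". SAEs that are both become SUSARs and go to the ethics committee within 15 days, or 7 if fatal or life-threatening.

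On the population, the Recruitment section states: "Mean age of Holocaust survivors attending the social club at Amcha centres is currently (in the year 2020) 89 years".

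**The concern.** Seriousness and expectedness are separate properties of an event. Seriousness describes the outcome and decides how fast the event is notified. Expectedness is a judgement on an event already notified and decides whether it goes on to the ethics committee. The section keeps them apart in its reporting steps but merges them in its definition.

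The practical risk lies in who applies the first test. The form is sent to the principal investigator, who according to the Randomisation section has no personal contact with participants. Whoever completes the form at a centre therefore has to decide whether the event was unexpected before the principal investigator hears of it. The SAE sentence gives that person no definition of the word and does not point to the one given later. With ten recruiting centres, the same event could be sent as an SAE from one and entered as an ordinary AE at another.

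**Working it through.** The check is logical. The section contains no figure to reproduce, and no power, rate or sample size enters.

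**Notation.** S = the event meets one of the listed outcomes; U = unexpected; R = related to a research procedure.

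**As written**
- SAE = S and U
- SUSAR = SAE and R and U = S and U and R

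The second U in the SUSAR line adds nothing, because it is already inside SAE. The principal investigator's expectedness assessment can have only one answer.

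**With expectedness removed from the definition**
- SAE = S
- SUSAR = S and R and U

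**Difference.** The SUSAR set is the same in both versions, provided that U means the same at both steps. The SAE set differs by exactly the events that are S but not U: serious and expected.

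**Does another clause bring those events back?**

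| Clause in the Adverse events section | Effect on a serious but expected event |
|---|---|
| SAE definition | Excludes it |
| Judgement clause | Does not clearly restore it: the clause is worded for important events that do not end in death or hospital admission |
| Recording whether expected or not | Attached only to non-serious AEs |
| General statement that all AEs are reported | Keeps the event on record as an AE, without SAE form or 24-hour notice |
| Exemption for planned admissions | Narrow; suggests that other admissions were meant to be notified |
| Principal investigator's assessment | Not reached, because the event was never notified as an SAE |

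**Are such events plausible?** The mean age of social club attenders is 89 years (Recruitment). The treatment phase is about 9 months and follow-up is 6 months after it (Design), so observation lasts about 9 + 6 = 15 months. Some deaths and admissions that staff would call foreseeable are plausible. The article gives no mortality or admission rate, so no count follows.

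**The case against.** The strongest reply is that this is a slip of drafting with little effect. Four points support it.

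1. The only definition of *unexpected* in the section is that the event is not on the protocol's list of expected occurrences, and the article shows no such list. If that meaning is carried back into the SAE sentence, no death or admission is shown to be excluded.
2. The rest of the section treats seriousness as a matter of outcome. A separate exemption for planned admissions would be largely unnecessary if foreseeable stays were already outside.
3. The events stay on record as AEs.
4. Reporting to the ethics committee concerns unexpected events in either case.

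Points 3 and 4 stand and limit the consequence. Points 1 and 2 make a slip likely, but they do not repair the text. The SAE sentence does not refer to the later definition, and in its ordinary sense the word leaves out foreseeable events. Staff completing forms follow the sentence in front of them.

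A reader might also infer that AE counts will differ by arm, because the Assessment of safety section says that "a case report form (CRF) will be completed after each information, assessment or therapy session" and only the life-review arm has therapy sessions. The documents do not support a conclusion from this. Suicidality screening is described as regular without restriction to an arm, AE reporting is not limited to occasions on which a CRF is completed, and the article states no between-arm comparison of AEs.

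**Conclusion.** The contradiction is real and can be seen from the section alone: unexpectedness cannot be both a condition for being an SAE and an open question about SAEs already notified. Read as written, a serious but expected event is handled only as an AE. SAE counts may therefore be incomplete, and they may be inconsistent between centres if staff read the word differently.

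The size is modest and cannot be put in numbers. It depends on how many serious events staff would regard as expected, on which the article gives nothing. The mean age of 89 describes social club attenders, not the randomised sample, which also draws on new members; it makes such events plausible and no more.

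Two stronger readings are tempting. One is that deaths would disappear from the safety record, so that an imbalance between arms could not be seen. The general reporting statement rules that out, since the deaths remain as AEs. The other is that a stated share of deaths would be misclassified. That would need both a mortality rate and the premise that every death counts as expected, and the article supplies neither.

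Sample size and efficacy analyses are unaffected. The correction is small but worth making, because the rule is wrong as it stands.

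**What to change.** In the Adverse events section, delete the words *and unexpected* from the SAE definition, so that seriousness rests on the listed outcomes alone. Keep relatedness and expectedness only in the principal investigator's later assessment, which defines SUSARs, and leave the existing definition of unexpected at that step. Events already recorded can be checked against the listed outcomes, so that any serious event entered only as an AE is reclassified.

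The cost is two words in the text and more SAE forms, since expected deaths and admissions would then be notified within 24 hours. The SUSAR definition, the ethics committee timelines and the exemption for planned admissions need no change.
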